### Pilot implementation of the risk screening tool

Study Aim 3 relies upon a well-established approach to the implementation of evidence-based practices, based on fundamental principles of organizational change developed by the Network for the Improvement of Addiction Treatment (NIATx) [28–30]. Of the approaches used to deliver the NIATx organizational change model, peer coaching has emerged as the most cost-effective option [28]. Members of the research team have adapted the peer coaching model employed by NIATx and applied it to promoting adoption of clinical guidelines for opioid prescribing in primary care [31]. Further adaptations will be made to tailor the approach for trauma settings. Peer coaches guide organizations through the change process by assessing workflows and identifying opportunities for improvement, and facilitating the plans, actions, analysis, and adoption of those improvements. This study will culminate with the pilot test of a strategy for implementing an opioid risk screening protocol in Wisconsin’s 4 largest trauma centers, using the novel opioid risk screening that was developed from the trauma patient data.

Implementation work will begin with observations of the UW Hospital Trauma Inpatient Service clinical workflows regarding the Alcohol Use Disorders Identification Test (AUDIT-C), a standardized alcohol use screening tool, a process which will inform potential implementation procedures for the opioid risk screen [32, 33]. This observation period will focus on when, where, and who is administering the AUDIT-C, how the information obtained from the AUDIT-C is recorded and communicated to the clinical care team, if and how that information guides clinical care decisions, and if and how an intervention or referral to treatment is conducted with the patient. Interviews will be conducted with UW Hospital Trauma Inpatient Service staff to assess how opioid risk screening could fit within the trauma inpatient workflow and how opioid-related interventions might best dovetail with that workflow. Nuances of the implementation model that are specific to a trauma service will be shared from the UW site to the four other pilot testing sites. The implementation model will be continuously refined based on the experience of each subsequent implementation, with emphasis placed on adjustments that are needed to tailor the implementation model for local organizational contexts.

### Statistical analyses

#### Aims 1 and 2: sample size calculations

Based on an expectation of an at-least 8% incidence in the sample over 24 weeks observation of opioid misuse or an opioid use disorder diagnosis, 221 participants would yield 80% power, at a 5% significance level, with a logistic regression to detect an odds ratio of 2.0 for a change of one standard deviation (SD) in score on the COMM. With a 25% drop-out rate expected, the study aims to recruit a total of 295 participants. While the current proposed work will not be adequately powered to attain significant findings regarding predictors of opioid overdose, examination of this outcome will constitute an exploratory aim.

#### Aims 1 and 2: analysis

The primary outcome event of this study will be a composite outcome indicating the development or lack of opioid misuse or opioid use disorder within 24 weeks of hospital discharge after traumatic injury. To assess the associations between patient factors and hypothesized risk factors with primary event, t-tests, Wilcoxon rank sum tests, and Chi square tests will be applied to measures that differ between those participants who achieve the primary event and those who do not. The test that is used will be based on numeric (normal or non-normal distribution) or a categorical factor. Any baseline or week 4 variable that is univariately associated with the primary event (p < 0.05) and does not reduce the number of events by more than 5% due to missing data will be considered a candidate variable to be included in the development of a best fit prediction model. The prediction model will be constructed based on a forward step-wise logistic regression model building process with threshold for entry into the model of significantly improving the model at a 0.05 significance level. Including baseline and week 4 variables will allow knowledge of which baseline variables are associated with future opioid misuse or opioid use disorder, and which variables can indicate the beginning of addiction in the hopes to develop a method to intervene before the onset of opioid misuse or opioid use disorder. To control for a possible early drug effect, time-on-opioids will be used as a covariate in the model. The diagnostic ability of the model will be assessed by constructing a receiver operating characteristic (ROC) curve and calculating the optimal sensitivity and specificity to predict primary event based on Youden’s J statistic [34]. A secondary survival analysis will examine variables that are associated with time-to-event, such as overdose or incident misuse detected on study measures.

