#### Administrative data sources

To assess hypothesized risk factors for opioid misuse or opioid use disorder, informed consent will give the study team permission to record personal health information from administrative records including the EMR, UW Health Trauma Registry, Wisconsin Circuit Court Access Program (CCAP), and Wisconsin PDMP Database. Administrative data sources include: emergency department notes and procedures from the EMR; Injury Severity Score (ISS) from the Trauma Registry [11], diagnosis codes from the EMR and trauma registry; concomitant medications, prescribed opioids, and other methods of pain management from the EMR and PDMP; and criminal activity from the CCAP. These data will be collected at week 24, at the conclusion of participant follow ups.

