### Primary outcome

The primary outcome is the development of opioid misuse or opioid use disorder during 24 weeks follow up, as measured by the Composite International Diagnostic Interview-Substance Abuse Module (CIDI-SAM) and/or the current opioid misuse measure (COMM).

The CIDI-SAM is a computer-assisted interview (average test–retest reliability *Κ* = 0.84) that identifies opioid use disorder presence and severity, based on symptom clusters, according to the 5th Edition of the Diagnostic and Statistical Manual of Mental Disorders. [10, 12, 13] The COMM is a 17-item paper survey with 5-point Likert scale response options, which will be used to identify the presence and severity opioid misuse behaviors. In order to determine changes in these behaviors over time, COMM will be administered at each follow up. The COMM has acceptable one-week test–retest reliability and internal validity (Intra-class Correlation Coefficient [ICC] = 0.86; 95% CI 0.77–0.92) [14, 15]. A raw score of greater than or equal to 9 will be considered positive for opioid misuse.

The composite outcome will be positive for participants with positive scores at week 24 on either the CIDI-SAM (opioid use disorder) or the COMM (opioid misuse), and will be negative for participations with neither.

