### Independent variables

A number of independent variables will be collected throughout the 24 weeks follow up. The inclusion of these measures are based on evidence from literature, and the surveys and interviews with Wisconsin trauma center staff and coordinators that were conducted as an earlier part of this study. The follow up time points were determined by the need to regularly evaluate for ongoing opioid use.

The baseline measures will be assessed for the development of a screening tool that could be administered at the point of care for a traumatic injury. Measures administered at follow up time points will be assessed for the development of a screening tool that could be administered by trauma staff at post-discharge follow up appointments or by primary care after a handoff from a trauma service to a clinical service.

Sociodemographic information (including age, sex, race, place of birth, work status, marital status, and household income and inhabitants) are collected at baseline. Additional baseline measures include: depression screen (PHQ-9); anxiety screen (GAD-7); Opioid Risk Tool (ORT); Social Support Questionnaire (ISEL-12); description of mechanism of injury; whether or not the injury was work related; number of procedures and/or complications associated with the injury; medication allergies; and time spent on an intensive care unit.

Ongoing opioid use after hospital discharge is recorded at each visit in order to establish a Morphine Equivalent Daily Dose (MEDD) per time point, as well as to determine the date of last opioid use.

The Pain Medication Questionnaire (PMQ) [16, 17] is a 23-item instrument assessing prescription use behaviors, whose score is associated with physician assessments of opioid medication risk. The instrument has excellent test–retest reliability (coefficient of stability 0.086); and acceptable internal consistency (Cronbach’s alpha = 0.73). This instrument is collected at each visit in an attempt to determine the optimal time for administering an opioid risk screening tool.

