## Discussion

The primary anticipation is that a parsimonious set of injury-related and historical factors will predict opioid misuse and the development of opioid use disorders during the period of observation and that these screening items are feasibly implemented during the course of the management of the injured patient. While it is not expected that these results will achieve adequate power to indicate statistically significant findings related to opioid overdose and mortality, collected patient factors may demonstrate trends toward predictive value for these outcome as well, which might be further developed in future study. The full project will develop 3 products: (1) a screening tool that describes patient opioid-related risk; (2) an implementation strategy for integrating the developed screening instrument into standard clinical care, and (3) preliminary strategies for interventions to prevent opioid misuse, overdose and addiction to be tested in future study, which will be informed by the AUDIT-C workflow analysis and by opioid-related risk factors identified by traumatic injury patient surveys.

While the primary purpose of the current work is the development of an effective opioid misuse screening tool, an important consideration during the course of the work will be imagining the form that an intervention aimed at preventing opioid misuse might take in future research. This intervention could manifest in a variety of forms, including something similar to ‘brief interventions.’ However, an effective intervention also might relate to effective management of pain, and/or appropriate prescribing and monitoring.

An additional question becomes “at what point should results of screening begin to affect care?” Clearly, appropriate and effective pain management is a primary concern during the acute hospital stay. Effective pain management reduces the likelihood of potentially catastrophic complications, such as pneumonia, heart attack, pulmonary embolism, impaired healing, and injury-related post-traumatic stress disorder [36].

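### One stepwise model pools baseline and week-4 predictors, week-4 COMM among them, although the article intends separate inpatient and post-discharge tools

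*Protocol article*

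**What the plan says.** **Intended tools.** The section Independent variables assigns baseline measures to a "screening tool that could be administered at the point of care for a traumatic injury". It assigns follow-up measures to a second tool, for post-discharge appointments or primary care. The Discussion expects that "a parsimonious set of injury-related and historical factors will predict opioid misuse" and that the items can be used while the injury is being managed. The section on pilot implementation plans staff interviews on how screening could fit the inpatient workflow.

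**Planned model.** Under Aims 1 and 2: analysis, the candidates are "Any baseline or week 4 variable that is univariately associated with the primary event" at p < 0.05, subject to a missing-data limit. "The prediction model will be constructed based on a forward step-wise logistic regression model building process", followed by one ROC curve and one Youden-optimal cut-off. In addition, "time-on-opioids will be used as a covariate in the model". The reason given for admitting week-4 variables is to learn "which variables can indicate the beginning of addiction in the hopes to develop a method to intervene before the onset" of misuse or disorder.

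**COMM.** Under Primary outcome, "COMM will be administered at each follow up", a score of 9 or more counts as misuse, and the composite is positive if either CIDI-SAM or COMM is positive at week 24. Table 1 shows COMM at weeks 4, 12 and 24, with no baseline entry. The sample size section powers the study on an odds ratio of 2.0 per SD of COMM score.

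**The concern.** The article describes two tools that differ in when they are used, but its analysis produces one model. A model for use in hospital may contain only what is known by discharge. Nothing in the analysis section enforces that for any model, so the tool handed to the Aim 3 pilot could contain items that an inpatient cannot yet answer.

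The second issue is what the accuracy figures would mean. Week-4 COMM is an earlier reading of an instrument that helps to define the outcome, and no rule addresses participants who are already positive at week 4. A pooled model cannot separate prediction before onset, which is the stated hope, from recognition of misuse that has already begun. Sensitivity, specificity and AUC would mix the two.

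**Working it through.** **1. When each instrument is first collected (Table 1)**

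| First collected | Instruments |
|---|---|
| Baseline | sociodemographics, MEDD, PMQ, PCL-5, PCS, AUDIT-C, CIDI-SAM, PHQ-9, GAD-7, ORT, ISEL-12 |
| Week 4 | ACE, COPE, COMM, OCS, PROMIS, PNI, PEG |

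Seven instruments start at week 4. ACE records childhood history and was placed at week 4 only to lighten the baseline survey, so it could be asked in hospital. The other six describe the patient's state after discharge. MEDD and PMQ are collected at both visits, so their week-4 readings are eligible as well.

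**2. Is week-4 COMM a candidate?** The analysis section does not name it, but its rule covers any week-4 variable and exempts none. The sample size section makes COMM the powered predictor. With no baseline COMM and candidates limited to baseline and week 4, the only eligible COMM score is the one at week 4.

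**3. The plan's own figures.** For one continuous covariate in logistic regression, two-sided 5% level, 80% power, event rate p = 0.08:

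n = (z₀.₉₇₅ + z₀.₈₀)² / [p(1 − p)(ln OR)²] = (1.960 + 0.842)² / (0.08 × 0.92 × 0.6931²) = 221.96

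This agrees with the stated 221 (power at 221 is 79.8%). Then 221 / 0.75 = 294.7, which gives 295. Expected events are 0.08 × 221 = 17.7. The sample size is not in dispute. It matters here because it confirms COMM as a predictor and gives the number of events.

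**4. Illustration of overlap.** The documents give no correlation between week-4 and week-24 COMM and no week-4 positivity rate, so both are assumptions. Let X (week 4) and Y (week 24) be standard normal with correlation r, and call the top 8% positive at each visit. The outcome is Y positive. Results by simulation:

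| r | Week-24 positives already positive at week 4 | AUC of X, all | AUC of X, week-4 negatives | Week-24 events left among week-4 negatives |
|---|---|---|---|---|
| 0.3 | 18.8% | 0.669 | 0.645 | 17.7 × 0.812 = 14.4 |
| 0.5 | 29.7% | 0.779 | 0.741 | 17.7 × 0.703 = 12.4 |
| 0.7 | 44.3% | 0.879 | 0.838 | 17.7 × 0.557 = 9.9 |

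The gap between the two AUC columns is the part of the apparent accuracy that comes from including people who already score positive. It is about 0.02 to 0.04. The share already positive is the larger effect. With 15% rather than 8% positive at week 4, that share is about 30% at r = 0.3 and 63% at r = 0.7.

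**The case against.** Four points can be made for the plan.

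- **Week-4 variables are included on purpose.** The article gives a reason and foresees post-discharge use, and separate fits by time point might be set out in a fuller document. The purpose is legitimate. But the article does state how the model is built, and that description does not carry out the two-tool intention stated earlier.
- **The problem is conditional.** The model is unusable in hospital only if a current-state week-4 item enters, or if the covariate, which is not defined, extends past discharge. This stands. A reader might infer that week-4 COMM is bound to enter first and crowd out the injury and historical items. The documents do not show that. The planned odds ratio of 2.0 is set for COMM itself and corresponds to r of about 0.33 and an AUC of about 0.69, which is no overwhelming advantage.
- **Week-4 COMM is not itself the outcome.** A reader might infer circularity from the analysis section's wording about development within 24 weeks. The operational definition under Primary outcome uses week-24 scores, so week-4 COMM is an earlier reading of a component. Persistence from week 4 to week 24 can also be a fair target for a post-discharge tool.
- **Court and prescription records.** A reader might infer that these are either shut out or leak later information, because "These data will be collected at week 24, at the conclusion of participant follow ups". That sentence dates the abstraction, not the events recorded. Neither reading is established, and the point should not be pressed.

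**Conclusion.** The point holds as a mismatch between sections. Two tools are intended and inpatient use is planned, but one pooled model is specified, and it admits week-4 COMM without a rule for participants already positive. That the resulting tool may be unusable during admission follows from the text under the stated condition and needs no numerical assumption.

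The size of the accuracy effect does rest on assumptions: correlations of 0.3 to 0.7, 8% positive at each visit, and a normal model. Under these, roughly one fifth to two fifths of the events being predicted would already be present at week 4, and the AUC of week-4 COMM is overstated by about 0.02 to 0.04 relative to those still negative. The sample size arithmetic is unaffected.

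**What to change.** In Aims 1 and 2: analysis, replace the single model with two.

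1. **Inpatient model (primary for the inpatient tool).** Candidates are limited to information obtainable by discharge: baseline measures, injury data, and historical items such as ACE. It has its own ROC curve and Youden cut-off, and it is the model used for any inpatient pilot. State what period time-on-opioids covers, and leave post-discharge use out of this model.
2. **Post-discharge model.** Week-4 predictors are allowed and the week-24 outcome is kept. As a sensitivity analysis, report accuracy among participants COMM-negative at week 4, or refit with COMM left out of the candidates.

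This uses the data already scheduled. ACE stays at week 4 for this cohort and can be treated as history. The costs are that the inpatient model's reported accuracy may be lower, and that the week-4-negative analysis is thin, with roughly 10 to 14 of about 18 events under the assumptions above. For that reason it belongs as a sensitivity analysis and should not replace the planned outcome.

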#### Participant surveys

Baseline visits will be completed during the inpatient stay or within 1 week of discharge, with follow-up visits at weeks 4, 12, and 24 after hospital discharge. Surveys will assess sociodemographic characteristics and health characteristics hypothesized to predict opioid use disorder risk that are not available in the EMR. The baseline and 24-week survey must be completed in person. The 4 and 12-week follow-up surveys were designed to be completed via mail, in-person, or by telephone. If participants complete all 4 visits, they will be compensated a total of $150, to be disbursed in increments at each visit. All study data will be transcribed from hard-copy questionnaires and source documents into a secure, web-based application for storing, managing, and analyzing study data.

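### At the planned event count, the 5% missing-data rule allows less than one missing case, so one or two missed week-4 surveys could exclude the week-4 survey scores together

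*Protocol article*

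**What the plan says.** Under Aims 1 and 2: analysis, a baseline or week-4 variable becomes a candidate for the forward stepwise logistic model if it meets two conditions. It must show a univariate association with the primary event at p < 0.05, and it must be one that "does not reduce the number of events by more than 5% due to missing data". The article does not restate the 5% as a count and gives no exception.

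The sample size section sets the scale: "Based on an expectation of an at-least 8% incidence in the sample over 24 weeks observation", and "221 participants would yield 80% power, at a 5% significance level", "to detect an odds ratio of 2.0 for a change of one standard deviation (SD) in score on the COMM". It continues: "With a 25% drop-out rate expected, the study aims to recruit a total of 295 participants".

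Under Primary outcome, the composite is scored from the week-24 CIDI-SAM and COMM, so events come from people who reached week 24. Table 1 lists nine measures at week 4: MEDD, PMQ, ACE, COPE, COMM, OCS, PROMIS, PNI and PEG. Only MEDD and PMQ also have a baseline entry. On collection, the Participant surveys section says: "The 4 and 12-week follow-up surveys were designed to be completed via mail, in-person, or by telephone". The baseline and week-24 surveys must be done in person.

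**The concern.** A 5% limit reads as a modest allowance for missing data. Applied to a count of events that is itself under 20, it allows none. Whether a predictor may be considered then turns on whether one particular participant, who later became a case, has a value for it.

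The week-4 measures are the exposed group because they are collected at one visit and go missing together. The analysis section includes week-4 variables in order to pick up early signs of addiction, and the Independent variables section plans a post-discharge screening tool from follow-up measures. Week 4 is the only point in the baseline-plus-week-4 pool at which COMM and ACE exist. If they are excluded, the reason would be one or two missed visits and not a lack of predictive value.

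**Working it through.** **Inputs.** From the sample size section: incidence of at least 8%, 221 analysable, odds ratio 2.0 per SD of COMM, 80% power, 5% significance, 25% drop-out, 295 recruited. From the analysis section: exclusion if more than 5% of events are lost. Week-4 non-response among cases is not given and is assumed below.

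**The plan's own figure.** For logistic regression with one continuous covariate (Hsieh's formula), two-sided:

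n = (1.960 + 0.842)² / [0.08 × 0.92 × (ln 2)²] = 221.96

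This is 222 against the stated 221; power at 221 is 79.8%. Drop-out: 221 / 0.75 = 294.7, rounded up to 295. The sample size stands, and 221 is the right base for counting events.

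**Tolerance of the rule.** Expected events = 221 × 0.08 = 17.68, and 5% of 17.68 = 0.884. One missing case costs:

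| Events | Loss from one missing case | Missing cases tolerated |
|---|---|---|
| 17 | 5.9% | 0 |
| 18 | 5.6% | 0 |
| 19 | 5.3% | 0 |
| 20 | 5.0% | 1 |
| 39 | 2.6% | 1 |
| 40 | 2.5% | 2 |

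Twenty events in 221 is an incidence of 20/221 = 9.05%; forty is 40/221 = 18.1%.

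**How likely the zero-tolerance range is.** With a binomial count in 221, the probability of 19 or fewer events is 68% at a true incidence of 8%, 29% at 10% and 7% at 12%.

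**Survival of the week-4 survey scores.** Let m be the assumed probability that a case misses week 4, independent of case status. With 18 events and none tolerated, survival is (1 − m)^18. With 22 events (10% of 221 = 22.1) and one tolerated, it is (1 − m)^22 + 22m(1 − m)^21.

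| m | 18 events | 22 events |
|---|---|---|
| 2% | 0.98^18 = 70% | 64.1% + 28.8% = 93% |
| 5% | 0.95^18 = 40% | 32.4% + 37.5% = 70% |
| 10% | 0.90^18 = 15% | 9.8% + 24.1% = 34% |

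**If nobody dropped out.** 295 × 0.08 = 23.6 events and 5% of that is 1.18, so one missing case would be tolerated and two would not.

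**The case against.** The arithmetic at 17 to 19 events is not in dispute, but several points limit it.

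- The 8% is a stated minimum. With 20 to 39 events one missing case is allowed. This stands, and it is why both event counts are shown.
- The missingness rates are assumptions. Cases are by construction people who attended at week 24, so the 25% drop-out does not carry over to their week-4 visit, and offering mail and telephone makes a missed week-4 survey less likely. This stands too: the low end of the range may be the realistic one.
- The week-4 group is not wholly at risk. Week-4 MEDD may be recoverable from the medical record or the prescription database, MEDD and PMQ also exist at baseline, and one missing item need not make a scale score missing. This stands, so the point is confined to survey scores lost through a missed visit.
- Protecting the number of events is a sensible aim when events limit the model, and the univariate screen already depends on the outcome. That is fair as to motive, but it does not make a tolerance of 0.88 of an event workable.

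Two stronger readings are tempting. A reader might infer that the whole model would shrink to a few fully observed items. The documents do not support this: the baseline survey is in person, many variables come from the medical record, trauma registry or prescription database, and nothing suggests appreciable baseline missingness among cases. A reader might also infer that, because the rule counts only events, a variable missing in half of the non-cases would pass. If missingness is independent of outcome, a half-missing variable passes at 18 events with probability 0.5^18, about 4 in a million. Otherwise the example needs strongly outcome-dependent missingness, for which the documents offer no mechanism.

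**Conclusion.** The concern holds in limited form. At the planning minimum the rule tolerates no missing case, and across the plausible range just above it (20 to 39 events) only one. The well-supported consequence is that the week-4 survey scores, COMM and ACE among them, could be excluded together because one or two cases missed a visit. How likely that is depends on the incidence reached and on a week-4 non-response rate that the documents do not give: on the assumed 2% to 10%, the chance of losing the scores runs from about 30% to 85% at 18 events and from about 7% to 66% at 22.

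This should be corrected before analysis because the filter decides what may enter the screening tool. It does not invalidate the study: the sample size is sound, the baseline and administrative predictors are little affected, and the problem lies in one clause that can be reworded.

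**What to change.** Replace the events-based condition with a pre-specified limit on each variable's overall missingness among analysed participants, set without reference to outcome. The cut-off is the sponsor's choice; 20%, for example, would be about 44 of 221 participants, so eligibility would no longer hang on one person. Handle the remaining missing predictor values by multiple imputation with the outcome in the imputation model, run selection and estimation on the imputed data, and keep the complete-case analysis as a sensitivity analysis.

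The cost is a change of wording and modest analysis time. The drawback is that stepwise selection across imputed datasets is somewhat more complex to code, and the way selections are combined has to be stated in advance. No change to recruitment, visits or instruments is needed.

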## Methods

### Primary aims

#### Aim 1

In a sample of traumatic injury victims (n = 295) at an American College of Surgeons, Level I trauma center, collect data on hypothesized risk factors for opioid misuse after traumatic injury, and monitor for the development of opioid use disorder during the 24 weeks follow up period.

#### Aim 2

Using the variables collected in Aim 1, develop a multivariate regression model of the proximal indicators that are most strongly associated with the development of opioid misuse or opioid use disorder (a composite outcome) after traumatic injury. Then, use this model to develop a parsimonious set of opioid risk screening items into a novel opioid risk screening tool which can be feasibly implemented at trauma centers.

#### Aim 3

Pilot test the implementation of the opioid risk screening tool at ACS Level I and II trauma centers in Wisconsin.

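### The ROC curve and cut-off come from a model containing time-on-opioids with no stated window, although post-discharge duration cannot be known when the point-of-care tool is used

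*Protocol article*

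**What the plan says.** The protocol article, under Aims 1 and 2: analysis, sets an entry rule for predictors: "Any baseline or week 4 variable that is univariately associated with the primary event (p < 0.05" being the threshold, with a limit on events lost to missing data). Forward stepwise logistic regression follows. One variable is then placed in the model without passing that rule: "To control for a possible early drug effect, time-on-opioids will be used as a covariate in the model". No window or definition is given. The next sentence takes the ROC curve, and the sensitivity and specificity at the Youden optimum, from the model. No version without the covariate is described.

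Under Independent variables, the article describes the follow-up data on opioid use: "Ongoing opioid use after hospital discharge is recorded at each visit in order to establish a Morphine Equivalent Daily Dose (MEDD) per time point". The same records serve a second purpose, stated there too: "as well as to determine the date of last opioid use". Table 1 shows these visits running to week 24. Under Primary outcome: "The composite outcome will be positive for participants with positive scores at week 24 on either the CIDI-SAM (opioid use disorder) or the COMM"; the COMM is the part that captures misuse.

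Two uses of the result are planned under Independent variables. The first is at the time of the injury, in a sentence quoted here without its last word: "The baseline measures will be assessed for the development of a screening tool that could be administered at the point of care for a traumatic". The second is a tool built from follow-up measures, for use by trauma staff or primary care after discharge. Aim 2 gives the goal: "develop a parsimonious set of opioid risk screening items into a novel opioid risk screening tool which can be feasibly implemented at trauma centers".

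**The concern.** Controlling for exposure is the reasoning of an explanatory analysis. A screening model has a different constraint: its performance must be estimated from information available when the patient is screened. At the inpatient point of care, time on opioids after discharge is zero for everyone and carries no information. A model that uses its later value has a discrimination, and a cut-off on its predicted risk, that the tool given at that moment cannot reproduce.

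A second problem depends on the definition. If duration is counted to the date of last use over all visits, it is complete only when the outcome is scored. Continued use at week 24 plausibly goes with a positive COMM or CIDI-SAM, so the model would be partly describing the outcome period rather than predicting it.

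At stake are the headline performance figures for Aim 2 and the threshold that could be carried into the four-centre pilot in Aim 3.

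**Working it through.** **1. The plan's own figure.** Inputs from the sample size section: incidence p = 0.08, odds ratio 2.0 per SD, 80% power, 5% significance (taken as two-sided), 25% drop-out. For logistic regression with one continuous covariate:

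n = (z₀.₉₇₅ + z₀.₈₀)² / [p(1 − p)(ln OR)²] = (1.960 + 0.842)² / (0.08 × 0.92 × 0.693²) = 221.96.

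The article states 221, at which power is 79.8%. Then 221 / 0.75 = 294.7, so 295. Both figures reproduce. Expected events are 0.08 × 221 = 17.7 among those evaluable. The sample size is not affected by this point.

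**2. The time points side by side.**

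| Element | When it is known |
|---|---|
| Candidate predictors | baseline or week 4 |
| Time-on-opioids | not stated; opioid-use data run to week 24 |
| Composite outcome | week 24 |
| Point-of-care tool | at the injury, before any post-discharge exposure |
| Post-discharge tool | at follow-up; duration to that date is known |

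Any window that extends past discharge is unavailable to the first tool. A window that extends past the screening date is unavailable to the second.

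**3. How much could it matter?** The documents give no distribution of duration and no association with the outcome, so this is an illustration only. Taken from the plan: 8% incidence and an odds ratio of 2.0 per SD, applied here to a generic screening score. Assumed: duration in non-events is exponential with mean 4 or 8 weeks, capped at 24; a share q of events is still on opioids at week 24; the remaining events follow the non-event distribution. A logistic model was fitted to 300,000 simulated subjects, and the AUC computed from its linear predictor.

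| Mean duration, non-events | q | Score alone | Score + duration to week 24 | Score + duration capped at week 4 |
|---|---|---|---|---|
| 4 weeks | 0 | 0.683 | 0.683 | 0.683 |
| 4 weeks | 0.25 | 0.683 | 0.738 | 0.695 |
| 4 weeks | 0.50 | 0.683 | 0.813 | 0.729 |
| 4 weeks | 0.75 | 0.683 | 0.901 | 0.790 |
| 8 weeks | 0 | 0.683 | 0.683 | 0.683 |
| 8 weeks | 0.25 | 0.683 | 0.722 | 0.689 |
| 8 weeks | 0.50 | 0.683 | 0.793 | 0.708 |
| 8 weeks | 0.75 | 0.683 | 0.878 | 0.743 |

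The gain is nil when duration is unrelated to the event. It reaches 0.901 − 0.683 = 0.218 at the extreme shown. With a week 4 cap the largest gain is 0.790 − 0.683 = 0.107, and a week 4 tool may properly claim that gain. The point-of-care tool may claim neither.

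**The case against.** The strongest reply is that the long window is inferred. The sentence gives its purpose as an early effect and sits beside a rule confined to baseline and week 4. The EMR and prescription-monitoring data listed under Administrative data sources would allow exposure to be cut at discharge or at week 4. A condensed article may leave a variable's definition to a fuller document. This stands: a reader might infer that time-on-opioids certainly runs to week 24, but the article does not say so, and the overlap with the outcome is conditional on that definition.

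Three other strong readings also fail.

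- Duration is not part of the outcome. The composite is a positive CIDI-SAM or COMM, and eligibility itself requires an expected need for outpatient opioids, so continued use is not an event.
- Duration is not always unknown at screening. For the post-discharge tool, duration up to the screening date is a legitimate predictor.
- The tool does not become unusable. Nothing says that every covariate must become a screening item.

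A reader might also quote the stand-alone AUC of an indicator for still using opioids at week 24. At 8% incidence this is 0.83 to 0.96 if 40% to 15% of participants still use and all events are among them, or 0.72 to 0.85 if 80% of events are. Those inputs are not in the documents, the indicator is not the planned covariate, and the figure is not the gain over the other predictors. Finally, the Background reports that pain, distress and pre-injury use predict longer opioid use, so adjustment could weaken items acting through duration. That is plausible, but the causal pathway is assumed, and a smaller coefficient is not in itself an error in a prediction model.

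What the reply does not answer is the point-of-care tool. Capping the window at week 4 does not help there. Week 4 variables are equally unknown at the bedside, but the article assigns follow-up measures to the second tool; it makes no such assignment for time-on-opioids. And if duration is left out of the tool, the ROC curve from a model containing it is not the tool's ROC curve.

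**Conclusion.** The concern holds in a limited form. The article commits to a covariate outside its own selection rule, without a window, and takes the reported performance and cut-off from the model that contains it. For the point-of-care tool this is a mismatch under any window that runs past discharge. For the post-discharge tool it is a mismatch only if the window runs past the screening date.

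Where there is a mismatch and duration is associated with the event, the reported AUC, sensitivity, specificity and cut-off would overstate what the screening items achieve. The size rests on two quantities the documents do not give, the window and the strength of association. The illustrative AUC of 0.683 against 0.72 to 0.90 (duration to week 24, q from 0.25 to 0.75) shows that it could be material, not that it is; it may be zero.

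**What to change.** Amend the one sentence under Aims 1 and 2: analysis so that the ROC curve and Youden cut-off for each tool come from either:

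- a model that uses only opioid exposure known when that tool is given: no post-discharge duration for the baseline tool, and at most discharge to week 4 for the week 4 tool; or
- a model without time-on-opioids.

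Report any model adjusted for total duration separately, labelled as exploratory. Settle this before the analysis, so that a threshold used in the pilot belongs to the items actually administered.

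The cost is a little more analysis work and possibly a lower reported AUC. No new data are needed, and the sample size of 295 does not change.
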